#### Group 3: INVEST – radio-physiology and stratification (guided treatment)

##### Radio-physiological investigations

Participants allocated to the INVEST arm will undergo standardised investigations (Table 3) prior to stratification of therapy. Routine NHS practice will apply in respect of women between menarche and menopause (that states that radiological examination, if justified, can be carried throughout the cycle until a period is missed). Participants randomised to this group who may potentially be pregnant will have a pregnancy test performed as per routine care. The investigations are shown in Table 3.

**Table 3 Tab3:** Investigations received by participants in group 3 (INVEST)

a. Anorectal manometry using high-resolution methods [80–82] will be used to determine defined abnormalities of recto-anal pressure gradient (see above for definition of functional defaecation disorder (FDD)) during simulated evacuation [37, 83, 84]. A standard high-resolution anal manometry (HRaM) system will be used with a standard laptop. Calibration, validation and maintenance of the equipment will follow the built-in programme and training manuals provided and will be recorded on the system at each session. Training on the system will be performed and documented in the investigator site file prior to sites commencing treatment
b. Balloon sensory testing using standardised methods [85, 86] (2 mL air per second to maximum 360 mL) will be used to determine volume inflated to first constant sensation, defaecatory desire and maximum tolerated volumes. Rectal hyposensation and hypersensation will be defined in accord to gender-specific normative data on 91 healthy adults [87]. The recto-anal inhibitory reflex will also be elicited by 50 mL rapid inflation (if necessary in 50-mL aliquots up to 150 mL)
c. A fixed-volume (50 mL) water-filled rectal balloon expulsion test [37, 70, 83] will be conducted in the seated position on a commode. Abnormal expulsion is defined as failure to expel with a 1-min effort for men and 1.5 min for women [88]
d. Whole gut transit study will use serial (different shaped) radio-opaque markers over 3 days with single plain radiograph at 120 h [89–91]
e. Fluoroscopic evacuation proctography will use rectal installation of barium porridge to defaecatory desire threshold (or maximum 300 mL) and evacuation on a radiolucent commode [90, 92–95] with preopacification of the small bowel (for enterocoele). Radiation dose, proportion of contrast evacuated and time taken will be recorded, as well as ‘functional’ (i.e. pelvic floor dyssynergia) and ‘structural’ features deemed obstructive to defaecation (e.g. rectocoele, enterocoele and intussusception) [37, 87, 96]. There is a maximum fluoroscopic screening time of 3 min

The results of these investigations will be sent to one of two designated investigators for analysis. A diagnosis of ‘functional defaecation disorder’ (FDD) will be made by assimilation of results from tests in Table 3 by an agreed protocol based on modified ROME III criteria [52]. These results will be reviewed centrally by two expert assessors independently using a secure data-sharing platform (2-week turnaround).

##### Modified Rome III criteria

Note: the updated ROME IV criteria were not available at the time of ethical approval for this study. However, our modified ROME III criteria take into account all investigative modalities (manometry, balloon expulsion and proctography: as Rome IV), and state:

Subjects must have, during repeated attempts to defaecate, evidence of impaired evacuation, based on either:Failed balloon expulsion test, and/orImpaired evacuation on proctography (failure to expel 65% contrast in 150 s),

with or without at least one of the following:Inappropriate contraction of the pelvic floor or less than 20% relaxation basal anal pressure on push manoeuvre (manometry) or proctographic evidence of failed puborectalis relaxation or paradoxical contraction; inadequate expulsive forces assessed by manometry or proctography.Abnormal pattern of anorectal manometry is defined as inappropriate contraction of pelvic floor or less than 20% relaxation basal anal pressure on push manoeuvre and/or inadequate expulsive forces.Based on the results of these investigations, participants diagnosed with FDD will undergo HTBF as above (group-2 interventions). Those without FDD will undergo HT only (group-1 interventions).The distribution of stratification factors in group 3, based on modified criteria for FDD [52], are met by approximately 50% of adult patients with CC based on UK data, and thus will be balanced in comparison with patients not receiving investigations. The allocation ratio will be monitored by the Data Monitoring Committee (DMC) (see below).

#### All three groups: concomitant care

Telephone support will be available from the therapist between visits (telephone number given, office hours only). In the instance of new psychological issues being determined during consultation, referral for psychological support will be deferred until after completion of behavioural interventions, except where there is clinical concern regarding the participant’s acute mental state requiring more urgent intervention (see below: withdrawal from treatment criteria).

#### Laxative use

All participants will be asked to discontinue laxative use at the first intervention visit and to refrain from using laxatives throughout the trial, as is standard UK practice in specialist biofeedback services. However, it is inevitable that participants will seek recourse to laxatives and other dietary supplements during the course of the programme. Experience shows that complete prohibition can lead to unreported laxative use, which might confound findings. Although we will strongly discourage ad libitum medication usage and specify a defined breakthrough regimen, we will record co-treatment with sufficient fidelity and integrity to enable use as covariates in analyses using a specific journal for this purpose (within the patient journal: see ‘Study Outcome Measures’). A concomitant medications list, including a shortlist of contributory or confounding medications, will be used to filter on data entry.

### Withdrawal criteria

Individual participants may be withdrawn from treatment in any of the following circumstances:Becomes pregnant or intends to become pregnant (only in baseline and intervention phases)Subsequently diagnosed with proven cause for secondary constipation, e.g. Parkinson’s disease or bowel obstructionRequires new medication with proven effects on bowel function, e.g. opioidsDevelops significant intercurrent illness precluding participationRequires surgery or other intervention (other than minor operations) during treatment phaseDevelops acute psychological problem causing safety concernElective withdrawal

All data collected up to the point of withdrawal from treatment will be used in the analyses and data will be collected at further time points unless participants specifically request otherwise. Participants may also request, at any point, no further follow-up visits or data collection.

### Strategies to improve adherence

Participants will be thoroughly counselled from the outset, detailing the study requirements and number of face-to-face treatment visits, the type and nature of all procedures and follow-up data collection visits, including all time commitments and responsibilities when taking part in the study. This will help to improve compliance with the protocol. Additional strategies to improve compliance include a visit window and tolerance of ±1 week and allowance for missing one of four treatment visits, and a follow-up time frame of 6 months without recourse to additional treatments to ensure the primary outcome remains uncontaminated. The participants may then move on to alternative treatments within the NHS routine care pathway or studies 2 or 3 within the CapaCiTY programme. Further strategies include reimbursement for patient travel at study milestones including baseline, 6-month and 12-month follow-up visits.

### Study outcome measures

#### Clinical endpoints

We have adopted a standardised outcome framework throughout the CapaCiTY programme. A set of standard clinical endpoints will be reported in this and the other studies that are part of the programme.

#### Primary clinical endpoint

Self-reported at 6 months after end of intervention:

Response to treatment defined as reduction in the Patient Assessment of Constipation–Quality of Life (PAC-QOL) score (Table 4) of at least 0.4 points [58–60].

**Table 4 Tab4:** Primary endpoint the Patient Assessment of Constipation–Quality of Life (PAC-QOL) score

The following questions are designed to measure the impact that constipation has had on your daily life over the past 2 weeks. For each question, please check one box.					
	Not at all - 1	A little bit - 2	Moderately - 3	Quite a bit - 4	Extremely - 5
The following questions ask about your symptoms related to constipation. During the past 2 weeks, to what extent or intensity have you…					
1. Felt bloated to the point of bursting?					
2. Felt heavy because of your constipation?					
The next few questions ask about how constipation affects your daily life. During the past 2 weeks, how much of the time have you…					
3. Felt any physical discomfort?					
4. Felt the need to have a bowel movement but not been able to?					
5. Been embarrassed to be with other people?					
6. Been eating less and less because of not being able to have bowel movements?					
The next few questions ask about how constipation affects your daily life. During the past 2 weeks, to what extent or intensity have you…					
7. Had to be careful about what you eat?					
8. Had a decreased appetite?					
9. Been worried about not being able to choose what you eat (for example, at a friend’s house)?					
10. Been embarrassed about staying in the bathroom for so long when you were away from home?					
11. Been embarrassed about having to go to the bathroom so often when you were away from home?					
12. Been worried about having to change your daily routine (for example, traveling, being away from home)?					
The next few questions ask about your feelings related to constipation. During the past 2 weeks, how much of the time have you…					
13. Felt irritable because of your condition?					
14. Been upset by your condition?					
15. Felt obsessed by your condition?					
16. Felt stressed by your condition?					
17. Felt less self-confident because of your condition?					
18. Felt in control of your situation?					
The next questions ask about your feelings related to constipation. During the past 2 weeks, to what extent or intensity have you…					
19. Been worried about not knowing when you are going to be able to have a bowel movement?					
20. Been worried about not being able to have a bowel movement?					
21. Been increasingly bothered by not being able to have a bowel movement?					
The next questions ask about your life with constipation. During the past 2 weeks, how much of the time have you…					
22. Been worried that your condition will get worse?					
23. Felt that your body was not working properly?					
24. Had fewer bowel movements than you would like?					
The next questions ask about your degree of satisfaction related to constipation. During the past 2 weeks, to what extent or intensity have you been…					
25. Satisfied with how often you have a bowel movement?					
26. Satisfied with the regularity of your bowel movements?					
27. Satisfied with the time it takes for food to pass through the intestines?					
28. Satisfied with your treatment?					

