**Methods/design:**

A three-arm, parallel-group, multicentre randomised controlled trial.

Objectives: to determine whether standardised specialist-led habit training plus pelvic floor retraining using computerised biofeedback is more clinically effective than standardised specialist-led habit training alone; to determine whether outcomes are improved by stratification based on prior investigation of anorectal and colonic pathophysiology. Primary outcome measure is response to treatment, defined as a 0.4-point (10% of scale) or greater reduction in Patient Assessment of Constipation–Quality of Life (PAC-QOL) score 6 months after the end of treatment. Other outcomes up to 12 months include symptoms, quality of life, health economics, psychological health and qualitative experience.

Hypotheses: (1) habit training (HT) with computer-assisted direct visual biofeedback (HTBF) results in an average reduction in PAC-QOL score of 0.4 points at 6 months compared to HT alone in unselected adults with CC, (2) stratification to either HT or HTBF informed by pathophysiological investigation (INVEST) results in an average 0.4-point reduction in PAC-QOL score at 6 months compared with treatment not directed by investigations (No-INVEST).

Inclusion: chronic constipation in adults (aged 18–70 years) defined by self-reported symptom duration of more than 6 months; failure of previous laxatives or prokinetics and diet and lifestyle modifications. Consenting participants (*n* = 394) will be randomised to one of three arms in an allocation ratio of 3:3:2: [1] habit training, [2] habit training and biofeedback or [3] investigation-led allocation to one of these arms. Analysis will be on an intention-to-treat basis.

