#### Secondary clinical endpoints

Self-reported at baseline and at 3, 6 and 12 months after end of intervention:Responses to treatment defined as a reduction in PAC-QOL score of at least 0.4 point [58–60]Binary responses to treatment defined as either a 1-point (or greater) reduction in PAC-QOL score [58–60]PAC-QOL: individual domains and total score (as continuous variables)Patient Assessment of Constipation–Symptoms (PAC-SYM) score [61]: individual domains and total score (as continuous variables)A 2-week patient diary (for 2 weeks prior to each assessment) to record bowel frequency and whether each evacuation was ‘spontaneous (no use of laxatives) and/or complete’; journal will also capture concurrent medication, health contacts, time away from normal activities (including work) since the patient’s last visitGeneric quality of life: the EuroQol Health Outcome Measure (EQ-5D-5 L) [62] descriptive system and the EuroQol Visual Analogue Scale (EQ-VAS) [63]NHS resource use: interventions, treatment sequelae and other health resource use related to the care of CCPatient costs related to constipation and the opportunity cost of time away from normal activitiesPatient Health Questionnaire-9 (PHQ-9) [64, 65]Generalised Anxiety Disorder Questionnaire (GAD-7) [66]Global study-specific patient satisfaction/improvement score (Visual Analogue Scale: VAS) and whether they would recommend each treatment experienced to other patientsPotentially modifiable cognitive and behavioural psychological variables shown to predict onset and perpetuation of other functional bowel symptoms: negative perfectionism [67], avoidant and ‘all or nothing’ behaviour subscales of the Behavioural Response to Illness Questionnaire [68] (CC-BRQ), and the Brief Illness Perception Questionnaire (BIPQ (CC)) [69]

A copy of trial outcome measures is available from the trial manager on request.

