### Sample size for the trial

The sample size has been calculated using the primary clinical outcome change in PAC-QOL score. A 0.4-point (10% of scale) reduction in PAC-QOL score [75–77] with a variance estimate conservatively set at a standard deviation (SD) = 1 will be considered clinically relevant.

To detect a mean change of 0.4 in PAC-QOL score (SD = 1) with 90% power and 5% significance level, 132 per arm or 264 participants in total will be required for the comparison of HT and HTBF (No-INVEST arm).

For the secondary comparison of INVEST versus No-INVEST a reduction of 0.4 points (SD = 1) will also be considered clinically meaningful. To detect an effect size of 0.4 with 90% power and at 5% significance level requires 90 participants in the INVEST arm assuming 264 participants have been recruited to the No-INVEST arm.

Allowing for a 10% loss to follow-up, a sample size of 147 is needed in the HT and HTBF arms and 100 in the INVEST arm. A total sample size of 394 patients across the three arms is required.

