### Statistical methods

#### Clinical outcomes analysis

The primary outcome will be analysed on intention-to-treat at the 6-month time point (prior to progressing to further condition-specific care). The average reduction in PAC-QOL score will be analysed using linear mixed-model regression with a random effect for centre and fixed effects for intervention, gender, baseline PAC-QOL and breakthrough medication.

Secondary outcomes will be analysed at 6-months and at additional time points (3 and 12 months from end of treatment) including the percentage of patients achieving a 1-point reduction. Outcomes will take the form of count (change in number of symptom episodes), ordinal (patient’s global impression of success) and continuous (questionnaire scores) data. Regression models, with a random effect for centre, appropriate to the outcome data types will be fitted to estimate the treatment effect, adjusting for baseline values (when appropriate), gender, and breakthrough medication use as a potential confounder.

Predictive modelling using baseline characteristics: measures of chronic pain, autonomic symptoms, joint hypermobility, cognitive, behavioural and mood variables share the common hypothesis that they are detrimental to the success of all treatments, i.e. they perpetuate illness in spite of therapy. Appropriate regression models will be developed to determine the influence of these pretreatment characteristics on the success of treatments.

Analysis will be performed using proprietary software (Stata, Stata Corp., College Station, TX, USA) by the appointed study statistician. *P* < 0.05 will be taken to indicate statistical significance. No analyses will be conducted until a statistical analysis plan (SAP) has been written and reviewed by an independent statistician. The SAP will be approved by the senior statistician and chief investigator. Multiple imputation will be used to address missing values. Subgroup analyses will be performed for selected baseline characteristics.

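### The primary endpoint is declared as a 0.4-point PAC-QOL response, but the hypotheses, sample size and primary analysis all use the mean score, so the stated 90% power does not apply to the declared endpoint

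*Protocol article*

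**What the plan says.** All references are to the protocol article.

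**Text that makes the primary outcome binary**
- Primary clinical endpoint: "Response to treatment defined as reduction in the Patient Assessment of Constipation–Quality of Life (PAC-QOL) score (Table 4) of at least 0.4 points".
- Abstract, Methods/design: "Primary outcome measure is response to treatment, defined as a 0.4-point (10% of scale) or greater reduction".

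**Text that makes it continuous**
- Abstract, first hypothesis: HTBF "results in an average reduction in PAC-QOL score of 0.4 points at 6 months compared to HT alone". The second hypothesis, on INVEST, is also framed as an average 0.4-point reduction.
- Sample size for the trial: "The sample size has been calculated using the primary clinical outcome change in PAC-QOL score", and then "To detect a mean change of 0.4 in PAC-QOL score (SD = 1) with 90% power and 5% significance level, 132 per arm".
- Clinical outcomes analysis, directly after a sentence on analysing the primary outcome: "The average reduction in PAC-QOL score will be analysed using linear mixed-model regression with a random effect for centre".

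**Text that lists both as secondary**
- The Secondary clinical endpoints, collected at baseline and at 3, 6 and 12 months, open with the 0.4-point response. Two items later comes "PAC-QOL: individual domains and total score (as continuous variables".
- For secondary outcomes, the analysis section names one responder percentage, the 1-point reduction. The data types it lists are count, ordinal and continuous; binary is not among them.

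**The concern.** A fall of at least 0.4 in one patient and a difference of 0.4 between two arm means are different quantities that share a number. Both arms could have high response rates without differing. The two comparisons can also fall on opposite sides of P < 0.05 in the same data.

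The document thus offers two candidates for the trial's main result. It declares one, and it sizes and analyses the other. Each is also on the secondary list at the primary time point. Patients and clinicians know the allocation and the outcome is self-reported, so the choice between the two should not be open when results are known. A reader who takes the endpoint section at its word will also attach the 90% power to a comparison for which it was not calculated.

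**Working it through.** **Inputs from the document.** Difference 0.4, SD 1, power 90%, significance level 5%, 132 evaluable per arm for HT v HTBF, 90 v 264 for INVEST v No-INVEST, 10% loss to follow-up. Sidedness is not stated; two-sided is used because it reproduces the stated number.

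**Assumptions, not from the document.** Change scores are normal, the SD of 1 applies to change, and the HT mean fall m takes values from 0 to 1.2.

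**1. Reproduce the plan's figure (mean change).**
- n per arm = 2(1.960 + 1.2816)² × 1² / 0.4² = 131.3, rounded up to 132. Power at 132 per arm is 90.1%.
- INVEST, 90 v 264: power 90.6%.
- Loss to follow-up: 132/0.9 = 146.7, so 147; 90/0.9 = 100. Total 147 + 147 + 100 = 394.

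Every stated figure is correct for the continuous score.

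**2. Apply the same design to the declared endpoint.** With mean falls m (HT) and m + 0.4 (HTBF), the response rates are
- HT: p1 = 1 − Φ(0.4 − m)
- HTBF: p2 = 1 − Φ(−m)

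Power = Φ{(p2 − p1 − 1.960·SE0)/SE1}, where SE0 uses the pooled proportion and SE1 the separate ones.

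Worked case, m = 0.2: p1 = 0.421, p2 = 0.579, difference 0.1585. SE0 = √(0.5 × 0.5 × 2/132) = 0.0615 and SE1 = 0.0608. Power = Φ{(0.1585 − 0.1206)/0.0608} = Φ(0.62) = 73.4%. This is the highest value at SD 1.

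| Assumed HT mean fall | Response, HT v HTBF | Power, 132 per arm | n per arm for 90% |
|---|---|---|---|
| 0 | 34.5% v 50.0% | 72.7% | 211 |
| 0.2 | 42.1% v 57.9% | 73.4% | 207 |
| 0.4 | 50.0% v 65.5% | 72.7% | 211 |
| 0.8 | 65.5% v 78.8% | 67.4% | 238 |
| 1.0 | 72.6% v 84.1% | 62.7% | 265 |
| 1.2 | 78.8% v 88.5% | 56.7% | 305 |

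With no loss to follow-up (147 per arm) the range is about 61% to 78%. For INVEST v No-INVEST (90 v 264) it is about 53% to 74%.

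**3. Sensitivity to the SD.** At SD 0.8 and 132 per arm, responder power is about 89% to 90% for HT mean falls of 0 to 0.4, and 66% at 1.2. Power for the mean rises as well: Φ(0.5/√(2/132) − 1.960) = 98%. The responder comparison remains the weaker of the two.

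**The case against.** The strongest reply is that the intention is clear and the endpoint sentences are the outlier. Hypotheses, sample size and primary model all use the mean, the caption of Table 4 calls the PAC-QOL score itself the primary endpoint, and the secondary list uses the word binary only for the 1-point response. This stands as evidence of what was probably meant, and it supports the direction of the fix. It does not remove the conflict: both endpoint statements set a threshold, and the continuous total score is listed separately as secondary.

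A reader might infer that the trial is underpowered, at 57% to 73% instead of 90%. The documents do not support that. No section plans a responder test as the primary analysis, and the analysis that is planned has its 90%. The lower end also needs an HT mean fall of 1.2 that appears nowhere, and the protocol itself describes its SD of 1 as conservative.

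A reader might also infer from the 34.5% response rate at zero mean change that the 0.4 cut-off classifies patients poorly. That does not follow. An SD of 1 may include real differences between patients in how much they changed, and the document gives no measurement-error figure.

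It can be said, finally, that a SAP will settle the matter. The protocol does bar outcome analyses until a SAP, prepared by people blinded to allocation, is signed off, and this limits the room for selective choice. But the article already fixes a binary endpoint, a continuous sample size and a linear model, so any SAP must depart from one of them. The generic secondary models, described as suited to the data type, could cover the 0.4-point response as a secondary outcome, but not as the primary one.

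**Conclusion.** The point holds as a contradiction in the current text about what the primary outcome is. The declared endpoint is binary; the powered and analysed endpoint is continuous; both are also listed as secondary at 6 months; and the response has no stated analysis as a primary outcome.

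The contradiction rests on the wording alone and needs no assumption. The power figures are an illustration. The ceiling of about 73% depends on normal change scores, SD 1 and a true difference of 0.4, but not on the HT mean. The 57% depends in addition on an assumed HT mean fall of 1.2. The sample size arithmetic is not at fault. The correction is needed because it decides what the trial's main result will be.

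**What to change.** - In the Abstract and the Primary clinical endpoint section, define the primary endpoint as PAC-QOL total score (change from baseline) 6 months after the end of treatment. State the estimate as the baseline-adjusted mean difference from the linear mixed model in the Clinical outcomes analysis section.
- Leave the 0.4-point response where it already stands, among the secondary endpoints. Name a binary model for it, for example a mixed logistic regression, and add binary to the listed data types.
- Remove the 6-month continuous total score from the secondary list. The domains, and the total score at 3 and 12 months, can stay.

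The change should be made before any outcome analysis. It costs a wording amendment and no patients or data: N stays at 394 and the 90% statement then applies to the declared endpoint. The registry record was not available for this review, so whether it needs the same change is unknown.

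The alternative is to keep the response as primary, with a binary primary model and a new sample size. On the assumptions above that means at least 207 evaluable per arm for HT v HTBF, or 207/0.9 = 230 randomised per arm against the planned 147, and the INVEST arm would need recalculating too.
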